### Management of the mass

The RMI is currently considered the standard diagnostic procedure. Therefore, in case of an RMI outcome of less than 200 – i.e., when a malignancy is not suspected- the mass is currently managed conservatively or with laparoscopy. In case of an RMI outcome of 200 or more the patient is managed together with a gynecological oncologist from the center hospital for comprehensive surgical staging and cytoreductive (debulking) surgery, according to prevailing guidelines.

However, it can be foreseen that conflicting results can occur between the RMI and the simple rules combined with the second stage test. If this is the case an individual risk assessment will be made and all conflicting results will be discussed with the patient, after which a gynecological oncologist will be consulted when deemed necessary. Although the RMI currently is considered standard care, we believe that conflicting results cannot be ignored.

### Reference standard

Histopathology is the clinical reference standard used in this study. Therefore, histology of the surgically removed adnexal masses is necessary. The resected masses will be classified according to the World Health Organization guidelines for histology [21]. The pathologist will not have access to the results of the index tests. The specimens obtained for histology will be stored for 30 years, according to prevailing guidelines from the Dutch society for pathology [22].

### Ethics and dissemination

The Medical Research Ethics Committee of the Maastricht University Medical Centre in The Netherlands has provided ethical approval for the conduct of the study. Written informed consent will be obtained from all patients before enrollment. The results of the study will be disseminated through international gynecological, radiological and/or oncological peer reviewed publications and conference presentations.

### Analysis

#### Sample size calculation

The RMI has a relatively low sensitivity (75–80 %). By reducing the amount of false negative test results the patient will benefit most in terms of prognosis and survival. For the calculation of the sample size we therefore focused on sensitivity as the most important primary objective.

This study is designed to have an 80 % power to detect an increase of sensitivity from 79 % for the RMI to 91 % for the two-step triage test with a two-sided α value of 0.05. Using a matched pair design, it can be estimated that the total discordance between the preoperative diagnosis and the final diagnosis based on histology, obtained by surgery, is 20 % (16 % and 4 % respectively). Based on McNemar’s test a minimum sample size of 97 women with a malignancy is required [23]. Taking a prevalence of malignancy of 40 % into account, the study will need 243 patients in total. To allow for loss of power of 10 % a total of 270 women will be enrolled in the study.

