### Objectives

The primary objective of the SUBSONiC-study (Simple Ultrasound Based ruleS to differentiate OvariaN Cysts) is to test the hypothesis that the simple rules, supplemented -in case of an inconclusive result- with either subjective assessment by an expert sonographer or MRI, will give better diagnostic accuracy than the RMI and therefore will improve the management of women with adnexal masses. Since the RMI is now widely used, any result in favor of the triage test has the potential to alter future clinical practice and reduce costs. Based on the results a cost-effectiveness analysis will be performed.

Secondary objectives are to perform subgroup-analyses for premenopausal and postmenopausal women and to compare the diagnostic accuracy of subjective assessment by an experienced ultrasound examiner with MRI for those cases where the simple ultrasound-based rules were inconclusive. Furthermore, the study aims to assess various forms of interobserver-agreement: in the interpretation of MRI images between radiologists; in the interpretation of simple ultrasound-based rules between the primary ultrasound and the expert ultrasound; and in the subjective assessment between the primary ultrasound and the expert ultrasound. Last objective is to perform translational research and validate new biomarkers in the diagnosis of ovarian cancer.

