### Study parameters

The primary research question is the comparison of diagnostic test accuracy between the currently used RMI and a new two-step triage system for the correct differentiation between malignant and benign adnexal masses. Main study parameters are sensitivity, specificity, positive predictive value, negative predictive value and positive and negative likelihood ratios. Sensitivity is defined as the percentage of women with ovarian cancer diagnosed with a malignancy by the RMI and the two-step test, respectively. The positive predictive value is defined as the percentage of patients with a positive test result having malignant disease. The final diagnosis will be based on histology (gold standard).

Based on the results, a cost-effectiveness analysis will be performed.

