#### Statistical analysis

We will use McNemar’s test to determine the statistical significance of differences in sensitivity and specificity between the RMI and the two-step test. For statistical purposes borderline tumors will be classified as malignant tumors. The 95 % confidence intervals for sensitivity and specificity will be obtained using Wilson’s interval method [24].

Receiver operating characteristic (ROC) curves will be generated using Medcalc software version 12.7.7.0 (MedCalc Software bvba, Ostend, Belgium) to illustrate the predictive value of the chance of malignancy when using the RMI, simple rules, subjective assessment and MRI. The method described by DeLong et al. will be used for the calculation of the difference between two AUCs [25].

For the subgroup analysis of pre- and postmenopausal women stratification will be applied.

The interobserver-agreement will be evaluated with Cohen’s kappa (kappa values of 0.81–1.0 indicate very good agreement, kappa values of 0.61–0.80 good agreement, kappa values of 0.41–0.60 moderate agreement, kappa values of 0.00-0.40 poor agreement) [26].

Two-tailed *P*-values of ≤ 0.05 will be considered statistically significant for all statistical comparisons.

The economic evaluation will explore the potential cost-effectiveness of the triage test compared to RMI. Incremental cost-effectiveness is expressed as difference in the number of correct diagnosis (i.e., either true positive or true negative for malignancy based on histology) between both methods. With the usual care (RMI) 83 % of all adnexal masses are diagnosed correctly, versus 96 % with simple rules. The consequences of the difference in correct diagnosed patients between the various test are recharged in the treatment (costs of surgical management and hospital stay following surgery) and will therefore lead to a difference in cost-effectiveness.

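### Better diagnostic accuracy is the claim, but no planned interval bounds a loss of specificity, and a non-significant McNemar test would not show that specificity is preserved

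*Protocol article*

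**What the plan says.** All references are to the protocol article.

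- **Objectives.** The hypothesis is that the two-step test "will give better diagnostic accuracy than the RMI and therefore will improve the management of women with adnexal masses".
- **Study parameters.** Sensitivity and specificity stand side by side: "Main study parameters are sensitivity, specificity, positive predictive value, negative predictive value and positive and negative likelihood ratios".
- **Sample size calculation.** Only sensitivity is powered, because fewer false negatives are said to benefit patients most: "we therefore focused on sensitivity as the most important primary objective". The target is "an increase of sensitivity from 79 % for the RMI to 91 % for the two-step triage test", with 80 % power and two-sided α of 0.05. This gives 97 women with a malignancy, 243 evaluable at 40 % prevalence, and 270 enrolled.
- **Statistical analysis.** McNemar's test is used "to determine the statistical significance of differences in sensitivity and specificity between the RMI and the two-step test", with two-tailed P ≤ 0.05 for all comparisons. The 95 % "confidence intervals for sensitivity and specificity will be obtained using Wilson"'s method. No interval is named for the paired difference in either measure, and nothing says what the two measures must show together.
- **Discussion.** A confirmed hypothesis is expected to influence guidelines and daily practice.

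**The concern.** Better accuracy is a statement about both kinds of error. Higher sensitivity bought with lower specificity may reflect no more than a lower threshold for calling a mass malignant. To support the wider claim, a reader needs to know how large a specificity loss the data still allow.

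The planned output answers this only if the McNemar test on specificity is significant in one direction or the other. If it is not, what remains is a P-value above 0.05 and two single-proportion intervals that ignore the pairing. Neither bounds the difference. The study could then report a significant sensitivity gain under the heading of better accuracy while the size of any rise in false positives stays unquantified.

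**Working it through.** **The plan's own figure.** Inputs from Sample size calculation: discordant proportions 0.16 and 0.04, so d = 0.12 and total discordance s = 0.20; two-sided α 0.05 (z = 1.960); 80 % power (z = 0.842). The conditional (Miettinen) formula is

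n = [1.960·s + 0.842·√(s² − d²(3 + s)/4)]² / (s·d²) = 99.0,

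close to the stated 97. Direct enumeration of the uncorrected McNemar test at n = 97 gives 79.5 % power. Then 97/0.40 = 242.5, rounded up to 243, and 243/0.9 = 270. The sample size is not in dispute.

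**Benign masses available.** 243 − 97 = 146 evaluable.

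**Assumption.** The article gives no discordance between the two tests among benign masses. A total discordance pd of 10, 15 and 20 % is used below.

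**Specificity loss that offsets the planned gain.** In correct diagnoses per woman, the gain is 0.12 × 0.40 = 0.048. The loss that cancels it is 0.048/0.60 = 0.08, or 8 points. Correct diagnoses are the outcome of the article's own economic evaluation.

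**Power of McNemar's test for a true loss δ** (normal approximation, n = 146): Φ[(δ√n − 1.96√pd)/√(pd − δ²)].

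**Expected half-width of a 95 % interval for the paired specificity difference** (true difference near zero): 1.96·√(pd/146).

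**Power to exclude a loss of margin m when there is no true loss:** Φ[m/√(pd/146) − 1.96].

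| Benign discordance | Power, 5-point loss | Power, 8-point loss | Half-width (points) | Power to exclude 5 points | Power to exclude 10 points |
|---|---|---|---|---|---|
| 10 % | 48 % | 87 % | 5.1 | 48 % | 97 % |
| 15 % | 34 % | 71 % | 6.3 | 34 % | 88 % |
| 20 % | 27 % | 58 % | 7.3 | 27 % | 77 % |

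A true 5-point loss would therefore give P > 0.05 in 52–73 % of such studies, and the offsetting 8-point loss in 13–42 %.

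**Why separate Wilson intervals do not fill the gap.** At the planned sensitivities, 77/97 gives 70–86 % and 88/97 gives 83–95 %. These overlap, although this is the difference that the paired test is sized to detect. At 146 benign masses, specificities near 85 % and 90 % give 78–90 % and 84–94 %. Each interval is valid for its own proportion; neither describes the contrast.

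**Size needed for a 5-point margin.** At 80 % power, (1.96 + 0.84)²·pd/0.05² gives 314 benign masses at 10 % discordance and 628 at 20 %. Dividing by 0.60 and then by 0.9 gives 583 to 1164 enrolled, against 270 planned.

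**The case against.** Several points on the other side are sound.

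- **The article does not say that P > 0.05 will be read as no loss, or that the claim will rest on sensitivity alone.** A reader might infer both from the priority given to sensitivity. The text supports neither; it leaves the non-significant case open.
- **McNemar's test is two-sided.** It can flag a loss, and a significant gain would itself show that specificity is preserved. The gap concerns the non-significant result only.
- **A specificity loss is not what the cited figures predict.** A reader might set the MRI specificity of 88 % against the RMI range of 85–90 % and expect one. But MRI serves only the roughly 20 % of masses that the simple rules leave inconclusive. If that split also holds among benign masses and the quoted values carry over, two-step specificity is 0.8 × 91 + 0.2 × 88 = 90.4 % with MRI, or 0.8 × 91 + 0.2 × 93 = 91.4 % with subjective assessment. Both lie slightly above the RMI range. A gain that small could still easily be non-significant: at a true 6-point gain, power is about 46–37 % at 15–20 % discordance.
- **Less overtreatment is not a planned conclusion.** The Discussion calls it an indirect hope and says the study is not powered for it.
- **Other outputs touch on specificity.** Predictive values, likelihood ratios and the count of correct diagnoses all reflect false positives, but the article names no interval for a between-test difference in any of them. The ROC comparison lists the component tests and the RMI, not the combined two-step test.
- **A margin or joint rule may stand in a full protocol or SAP not shown.** Its absence from the article is therefore not the point. The point is that the test and interval method which the article does name do not bound the paired difference.

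**Conclusion.** The point stands in a limited form. The analysis stated in the article yields no bound on a paired specificity loss, so a non-significant specificity test could not support the wider accuracy claim. With 146 evaluable benign masses and an assumed discordance of 10–20 %, power is 48–27 % for a 5-point loss and 87–58 % for the 8-point loss that would cancel the planned sensitivity gain at 40 % prevalence. These figures depend on the assumed discordance and on the article's prevalence.

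McNemar's test and the Wilson intervals are not wrong for what they do, and the 97/243/270 calculation is unaffected. Nor do the documents show that specificity will fall. The finding is an inexpensive improvement that should be made. It does not depend on adopting a fixed margin, which is a trade-off for the investigators.

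**What to change.** In Statistical analysis, keep McNemar's test and the Wilson intervals, and add:

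1. The paired differences (two-step minus RMI) in sensitivity among malignant masses and in specificity among benign masses, each with a 95 % paired score interval (Tango or Newcombe). The expected half-width for specificity is about 5–7 points.
2. A statement that a non-significant specificity test will not be read as preserved specificity.
3. A wording rule: the conclusion is higher sensitivity, reported beside the interval for the specificity difference, unless that interval supports the wider accuracy claim.

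If the investigators want a formal margin, they should choose it before analysis and know its limits. A 10-point margin has 97–77 % power at 10–20 % discordance if there is no true loss. It exceeds the 8-point break-even, however, so meeting it would not exclude a net fall in correct diagnoses. A 5-point margin is out of reach at the present size.

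The cost is a little more analysis and possibly a narrower headline claim. No patients or procedures are added.

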#### Statistical analysis

We will use McNemar’s test to determine the statistical significance of differences in sensitivity and specificity between the RMI and the two-step test. For statistical purposes borderline tumors will be classified as malignant tumors. The 95 % confidence intervals for sensitivity and specificity will be obtained using Wilson’s interval method [24].

Receiver operating characteristic (ROC) curves will be generated using Medcalc software version 12.7.7.0 (MedCalc Software bvba, Ostend, Belgium) to illustrate the predictive value of the chance of malignancy when using the RMI, simple rules, subjective assessment and MRI. The method described by DeLong et al. will be used for the calculation of the difference between two AUCs [25].

For the subgroup analysis of pre- and postmenopausal women stratification will be applied.

The interobserver-agreement will be evaluated with Cohen’s kappa (kappa values of 0.81–1.0 indicate very good agreement, kappa values of 0.61–0.80 good agreement, kappa values of 0.41–0.60 moderate agreement, kappa values of 0.00-0.40 poor agreement) [26].

Two-tailed *P*-values of ≤ 0.05 will be considered statistically significant for all statistical comparisons.

The economic evaluation will explore the potential cost-effectiveness of the triage test compared to RMI. Incremental cost-effectiveness is expressed as difference in the number of correct diagnosis (i.e., either true positive or true negative for malignancy based on histology) between both methods. With the usual care (RMI) 83 % of all adnexal masses are diagnosed correctly, versus 96 % with simple rules. The consequences of the difference in correct diagnosed patients between the various test are recharged in the treatment (costs of surgical management and hospital stay following surgery) and will therefore lead to a difference in cost-effectiveness.

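### No single test decides the primary hypothesis: sensitivity and specificity are each tested at the full two-sided 0.05

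*Protocol article*

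**What the plan says.** - **Hypothesis.** Objectives and Discussion both state that the two-step test will show better diagnostic accuracy than the RMI. Neither says which measure of accuracy decides.
- **Study parameters.** Under the primary research question, six measures stand side by side: "Main study parameters are sensitivity, specificity, positive predictive value, negative predictive value and positive and negative likelihood ratios".
- **Sample size calculation.** Here sensitivity is put first: "we therefore focused on sensitivity as the most important primary objective". The reason given is that fewer false negatives benefit the patient most. The study is sized for "80 % power to detect an increase of sensitivity from 79 % for the RMI to 91 % for the two-step triage test". The alpha used there is 0.05, two-sided.
- **Statistical analysis.** The planned comparison uses "McNemar’s test to determine the statistical significance of differences in sensitivity and specificity between the RMI and the two-step test". The threshold then covers everything: "Two-tailed *P*-values of ≤ 0.05 will be considered statistically significant for all statistical comparisons".
- **Subgroups.** Objectives lists the pre- and postmenopausal analyses as secondary. Statistical analysis adds only that they will be stratified.

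**The concern.** A reader who applies the Statistical analysis section as written finds two tests with equal standing and the same threshold, and a hypothesis that either could be said to confirm. The priority given to sensitivity is stated when the study is sized and is not repeated where the measures are listed or where the tests are defined. Calling sensitivity the most important primary objective also implies that there are others.

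Two things are at stake. First, under an either-or reading the error rate of the main claim is not the two-sided 0.05 on which the sample size rests. Second, sensitivity and specificity can move in opposite directions. A significant specificity gain could be presented as better accuracy when sensitivity shows no gain or falls, although sensitivity is the only measure the study is sized for. The Discussion expects a confirmed hypothesis to affect guidelines, so the deciding result should be fixed in advance.

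**Working it through.** **Inputs from the protocol article.** Two-sided alpha 0.05; power 80%; discordant proportions 16% and 4% (total 20%); 97 women with a malignancy; prevalence 40%; 10% allowance; 243 and then 270 women (Sample size calculation). Two McNemar tests, each at 0.05 (Statistical analysis).

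**1. The plan's own figure.** With P = 0.16/0.20 = 0.8, the conditional McNemar formula gives the number of discordant pairs:

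m = (1.96/2 + 0.8416 × √(0.8 × 0.2))² / (0.8 - 0.5)² = (0.980 + 0.337)² / 0.09 ≈ 19.26.

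Then 19.26/0.20 = 96.3, rounded up to 97; 97/0.40 = 242.5, rounded up to 243; 243/0.90 = 270. The stated figures reproduce. They rest on one test, sensitivity, at two-sided 0.05.

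**2. Independence of the two tests.** Sensitivity is compared in women with malignant histology and specificity in women with benign histology. No woman contributes to both, so the two tests are independent.

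**3. Error if either test may support the claim, both true differences being zero.**

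| Event | Sensitivity alone decides | Either may decide |
|---|---|---|
| Any rejection, either direction | 5% | 1 - 0.95² = 9.75% |
| False claim that triage is better | 2.5% | 1 - 0.975² = 4.94% |

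The excess in the second row is the chance that specificity falsely favours triage while sensitivity does not: 0.975 × 0.025 = 2.44%. Added to 2.5%, this gives 4.94%.

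**4. Simulated McNemar tests.** The full 270 women are used: 0.40 × 270 = 108 malignant and 162 benign. The discordance when the tests are equally accurate is not in the document; 10% to 20% is assumed.

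| Version of McNemar's test | Sensitivity alone, either direction | Either test, either direction | Either test, false claim of better |
|---|---|---|---|
| Uncorrected | 4.3-5.4% | 9.0-10.3% | 4.5-5.2% |
| Exact or continuity-corrected | 2.2-3.0% | 4.6-6.1% | 2.3-3.1% |

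The article does not say which version will be used. The conservative versions start from a lower rate for the single test. Allowing either test still roughly doubles that rate, but the total stays close to the nominal level.

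**The case against.** **Sensitivity is already ranked first.** The sample size section gives a clinical reason for the ranking as well as a numerical one. This stands in part: it would be wrong to say the protocol has no priority among its measures. What is missing is a testing rule that uses the priority.

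**Either-or is only one reading.** The hypothesis could also be decided by sensitivity alone, or by requiring both measures, and neither of those inflates the error. That is correct, and the rates above are conditional on the either-or reading. The defect is that the text does not choose between the readings.

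**The analysis plan may settle it.** A condensed article commonly leaves the testing order to another document. Here, however, the article sets a rule: P-values at or below 0.05 "will be considered statistically significant for all statistical comparisons". A later hierarchy would have to qualify that sentence.

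**Stronger readings that the document does not support.**
- A reader might take 9.75% as the chance of falsely declaring triage better. It counts rejections in both directions, including those in favour of the RMI. For the directional claim the figure is about 4.9%.
- A reader might add the menopausal subgroup tests and reach a much larger rate. Those analyses are secondary objectives, and nothing lets a subgroup result decide the primary hypothesis.
- A reader might treat "any result in favor of the triage test has the potential to alter future clinical practice and reduce costs" in Objectives as a success rule. In context it explains why the study is worth doing, and the Discussion ties a change of practice to confirmation of the hypothesis.

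**Sensitivity alone is a poor sole criterion.** A test that labels more masses malignant gains sensitivity and loses specificity. This stands, and the remedy has to include a safeguard on specificity.

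**Conclusion.** The point holds in a limited form. The protocol article does not fix whether sensitivity, either measure or both must succeed for better diagnostic accuracy to be claimed, and its significance sentence gives both tests the full 0.05. If either may carry the claim, the error roughly doubles: 9.75% against 5% in either direction, or about 4.9% against 2.5% for a false claim that triage is better. With an exact or continuity-corrected test the totals are about 4.6-6.1% and 2.3-3.1%.

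These figures assume no true difference in either measure. The simulated ranges also assume full enrolment at 40% prevalence and a discordance of 10-20%. The inflation is moderate. The more practical risk is that a specificity gain is used to support the claim when the powered sensitivity comparison has failed. This should be corrected, but it does not affect the validity of the sample size calculation.

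**What to change.** 1. In Study parameters and Statistical analysis, state that the sensitivity difference between the two-step test and the RMI (McNemar, two-sided 0.05) is the single primary test.
2. Test specificity confirmatorily, at two-sided 0.05, only if sensitivity is significant in favour of triage.
3. Report the specificity difference with its 95% CI whatever the sensitivity result. Do not claim better overall accuracy if specificity is significantly worse.
4. Limit the P ≤ 0.05 sentence to these two tests. Label predictive values, likelihood ratios, AUC comparisons and menopausal subgroups as exploratory.

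This follows the priority already given in the sample size section. The cost is wording only: 97, 243 and 270 are unchanged, because they were derived for the sensitivity test at two-sided 0.05. The small downside is that a specificity gain cannot be claimed as confirmatory if the sensitivity test fails.
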